### Sample size

According to a previous systematic review [29] that compared the therapeutic effects of acupuncture, lactulose, and sham acupuncture for FC, the mean weekly improvement in SBMs of 2.46, 2.17, and 1.76 were found in the verum acupuncture, lactulose, and sham acupuncture group, respectively. We anticipate a mean weekly SBM improvement of 2.5 in the verum acupuncture group, 2.2 in the PEG 4000 group, 1.8 in the sham acupuncture group, and 0.9 in the waiting-list control group. Considering α = 0.05, 1-β = 0.8, and a standard deviation of 2.0, a sample size of 128 is needed, with a drop-out rate of 10%; a total of 140 FC patients will be finally recruited.

Based on previous neuroimaging studies [30, 31], 12–15 individuals in each group is the reasonable sample size for stable cerebral responses. Therefore, in this trial, 15 participants randomly selected from each group will be scanned by MRI and PET-CT.

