#### Group D

During the treatment period, no intervention will be performed on this group; however, it has been promised that these participants will receive 10 sessions of acupuncture therapy at the end of the trial, similar to the participants in group A.

Participants with fainting, infection, severe diarrhea, dehydration, or other severe adverse events should be discontinued from treatment and processed immediately. During the treatment period, participants are usually not allowed to use concomitant care and interventions. However, if required, participants will be permitted to use extra osmotic laxatives; the type and dosage of medication used should be recorded in the case report form (CRF). If patients take concomitant care and interventions more than three times in the treatment period, they will be defined as non-adherent and will not be enrolled into the statistical analysis.

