#### Self-rating Anxiety Scale (SAS) and Self-rating Depression Scale (SDS)

Anxiety and depression are emotional disorders commonly accompanied by FGIDs [40]. Hence, the SAS [41] and SDS [42] are used to assess the emotional health of FC patients.

In addition, the heart rate variability (HRV) will be measured by dynamic electrocardiogram to evaluate the activity of the autonomic nervous system of FC patients [14].

The above outcomes will be assessed at baseline and at the end of treatment/waiting. In addition, the stool diary and CCS will also be evaluated at mid-point. The expectation for efficacy in each patient will be evaluated at baseline.

All the outcome assessments will be performed by independent outcome assessors. These assessors are trained before participating in this trial and blinded to the randomization.

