### Data analysis

#### Clinical data analysis

The clinical data will be analyzed using SPSS 20.0 statistics software (IBM Co., Armonk, NY, USA) based on the per-protocol (PP) principle. Continuous variables on normal distribution will be described with means and standard deviation (SD). Continuous variables conforming to a skewed distribution will be described with median and inter-quartile range. Categorical variables will be described with percentages (%).

Clinical data from the four groups will be compared using one-way ANOVA; statistical analysis between two groups (group A and B, group A and C, group A and D) will be performed using Dunnett’s test. The comparison between baseline and end of treatment in each group will be carried out with a paired samples *t*-test. The clinical outcome stool diary and CCS scores will be compared at three timepoints using the repeated measures ANOVA. Clinical data on skewed distribution will be compared using a non-parametric test. Categorical variables will be compared using the *χ*^2^ test or Fisher’s exact test. The statistical significance threshold is set at 0.05 with the two-sided test.

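### The three-timepoint repeated measures ANOVA drops every patient with one missing value, discarding observed weeks; a mixed model would keep them and is valid under missing at random

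*Protocol article*

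**What the plan says.** All places are in the protocol article.

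- **Clinical data analysis, longitudinal method:** "The clinical outcome stool diary and CCS scores will be compared at three timepoints using the repeated measures ANOVA". The software is SPSS 20.0.
- **Clinical data analysis, between-arm method:** "Clinical data from the four groups will be compared using one-way ANOVA", followed by Dunnett's test of verum acupuncture (A) against sham (B), PEG 4000 (C) and waiting list (D). Skewed data go to a non-parametric test.
- **Clinical data analysis, analysis set:** the work is done "based on the per-protocol (PP) principle".
- **Group D:** of patients who use concomitant care more than three times in the treatment period, the text says "they will be defined as non-adherent and will not be enrolled into the statistical analysis".
- **Outcomes, end of the SAS and SDS section:** all outcomes are taken at baseline and end, and "the stool diary and CCS will also be evaluated at mid-point". No other outcome is given a mid-point.
- **Sample size:** "Considering α = 0.05, 1-β = 0.8, and a standard deviation of 2.0, a sample size of 128 is needed", and the total of 140 is reached "with a drop-out rate of 10" per cent.

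The article names no imputation and no likelihood-based method for a missed visit.

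**The concern.** Repeated measures ANOVA, as ordinarily run, works on one complete row per patient. A patient who leaves after week 1 loses the mid-point value already recorded. A patient who misses only the mid-point loses the end value as well. The plan expects loss and adds the mid-point for just these two outcomes, so it collects partial data that its named method cannot use.

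Two things are at stake. The first is precision, together with consistency: a patient who misses only the mid-point stays in the end-of-treatment ANOVA and Dunnett comparisons but is absent from the repeated measures analysis of the same outcome. The second is bias. If poor week-1 responders leave more often, more of them leave the weaker arms, the patients who remain there look better than the arm as a whole, and the verum differences shrink. The stool diary holds the weekly SBMs on which the trial is sized, so this is not a minor outcome.

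**Working it through.** **1. The plan's own figure.** Inputs from Sample size: mean improvements 2.5, 2.2, 1.8 and 0.9 SBMs per week, SD 2.0, alpha 0.05, power 0.80.

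- Grand mean = (2.5 + 2.2 + 1.8 + 0.9)/4 = 1.85.
- Mean squared deviation = (0.4225 + 0.1225 + 0.0025 + 0.9025)/4 = 0.3625.
- f² = 0.3625/2.0² = 0.0906, so f = 0.301.
- Noncentral F with 3 and N − 4 degrees of freedom and noncentrality N × f²: at N = 128 (noncentrality 11.6) the power is 81.3%. This is the first balanced design to reach 80%, so the stated 128 is reproduced.

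**2. What deletion costs in power.** At the planned 10% loss, 140 × 0.90 = 126 patients remain. Noncentrality is 126 × 0.0906 = 11.4 and power is 80.6%. The target is still met.

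**3. How many patients deletion removes.** If mid-point and end are each missed independently with probability p, the share deleted is 1 − (1 − p)².

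- p = 0.05: 1 − 0.9025 = 9.75%, leaving about 126 of 140.
- p = 0.10: 1 − 0.81 = 19%, leaving about 113 of 140.

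The values of p are assumptions; the article gives only an overall 10%.

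**4. Bias when loss depends on the week-1 value.** The documents do not fix the loss pattern, the correlations or the mid-point effect, so these results are illustrative. The true A minus D difference is 2.5 − 0.9 = 1.60; the true A minus B difference is 2.5 − 1.8 = 0.70.

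| Assumed setting | Complete cases, A − D | Likelihood (mixed model), A − D |
|---|---|---|
| Change scores; mid–end correlation 0.7; mid-point effect 70% of end effect; loss about 10–11% in A and 15–20% in D | 1.44 to 1.53 | 1.59 to 1.60 |
| Baseline mean 2; half the gain by week 1; correlations 0.5 (baseline–mid), 0.7 (mid–end), 0.35 (baseline–end); loss 10% on average | 1.58 | 1.60 |
| Same, but all correlations 0.5 | 1.60 | 1.60 |

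In the first setting, A − B is 0.64 to 0.67 for complete cases and 0.69 to 0.70 for likelihood. In the third there is no bias, because selection on the week-1 value shifts baseline and end equally and the change is unaffected.

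**5. Size against the noise.** The standard error of a two-arm difference at 32 per arm is 2.0 × √(2/32) = 0.5. The A − D bias therefore runs from 0.02/0.5 = 0.04 to 0.16/0.5 = 0.32 standard errors, and the A − B bias from 0.03/0.5 = 0.06 to 0.06/0.5 = 0.12.

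**6. Other loss mechanisms**, in the second setting:

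- Loss unrelated to response: 1.60 by both methods.
- Loss depending on the unseen end value: complete cases 1.45, mixed model 1.46.

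**7. Interaction with the per-protocol rule.** If the same patients are first removed by that rule, the mixed model sees only the complete cases and returns their answer (1.58 for loss depending on week 1, 1.45 for loss depending on the unseen end value).

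**The case against.** The strongest objection is that the main between-arm comparison is not this analysis. One-way ANOVA and Dunnett's test carry A–B, A–C and A–D, and an end-of-treatment comparison does not need the mid-point. That stands. A reader might infer that all the verum contrasts in the plan rest on deleted data; the documents support this only for the three-timepoint analysis.

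A reader might also infer that deletion leaves the trial underpowered, since about 113 patients would give roughly 76%. That figure applies a one-way F-test, which does not require the mid-point, to a loss nearly double the one planned. At the plan's own 10% the target is met, and the 14 patients lost are already budgeted for.

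A third tempting reading is that a mixed model removes the bias. Steps 4 and 6 show that it does so only when loss depends on observed values. With loss unrelated to response there is nothing to remove; with loss depending on the unseen end value nearly all of it stays.

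It is also fair that the waiting list is promised acupuncture afterwards, an incentive to stay, and that the full protocol or SAP may deal with missing visits. Case deletion is the usual behaviour of the named method, not something the article states. But the article does fix the method, so the point concerns a choice and not an omission.

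Finally, the per-protocol exclusion acts first and a change of model cannot undo it. That is correct, and it limits the gain. It does not cancel it: the article's one stated exclusion concerns concomitant care, so patients who merely miss a visit can remain in the set and would still be dropped by this ANOVA. Conversely, moving to all randomised patients without changing the method would bring the analysis back to complete cases.

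**Conclusion.** The point holds in limited form. The named method drops any patient lacking one of three values, wastes observed weeks, and can put this analysis on a different set of patients from the end-of-treatment tests. The certain cost is precision. The possible cost is a modest bias towards no difference: verum minus waiting list of about 1.44 to 1.58 against 1.60 where loss depends on the week-1 response, and none at all under some correlation patterns. These sizes rest on assumed loss rates, correlations and mid-point effects, and cannot be derived from the documents. No power shortfall is claimed. The change is worth making because it is a cheap improvement to a stated method for the outcome that sizes the trial.

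**What to change.** In Clinical data analysis, replace the repeated measures ANOVA for approximately normal outcomes by a linear mixed model for repeated measures:

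- outcome: the mid-point and end values, using all that are available;
- terms: arm, week, arm-by-week, baseline value and baseline-by-week;
- unstructured covariance, fitted by restricted maximum likelihood;
- A–B, A–C and A–D contrasts at end of treatment read from the model with a Dunnett-type adjustment.

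State that the model assumes missing at random, and add a sensitivity analysis for loss that depends on unseen values. Fit it to all randomised patients to obtain the full benefit. Within the per-protocol set it still keeps a patient who misses one of the two post-baseline visits. It recovers nothing from a patient with no post-baseline value.

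The cost is a few sentences and slightly more analysis work. No new data are needed, and SPSS 20.0 can fit the model. The model relies on approximate normality, so the planned non-parametric test should stay for skewed items such as the 0–3 straining score. Because it adjusts for baseline, its estimates can differ somewhat from unadjusted ones even with complete data.

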**Methods:**

This is a multimodal neuroimaging randomized controlled trial. In total, 140 FC patients will be randomly allocated into four groups: the verum acupuncture group; the sham acupuncture group; the PEG 4000 group; and the waiting-list group. This trial will include a two-week baseline period and a two-week treatment period. Patients will receive 10 sessions of acupuncture, sham acupuncture, PEG 4000, or no intervention during the treatment period. The stool diary, Cleveland Constipation Score (CCS), Patient Assessment of Constipation Symptom (PAC-SYM), and Patient Assessment of Constipation Quality of Life Questionnaire (PAC-QoL) will be used to assess the clinical efficacy of different interventions. The MRI and PET-CT scans will be performed to detect cerebral functional changes in 15 patients in each group at baseline and at the end of treatment/waiting. Multimodal imaging data will be associated with clinical data to investigate possible correlation between brain activity changes elicited by different interventions and symptoms improvement.

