### Outcomes

#### Stool diary

The stool diary contains three domains: weekly SBMs; stool feature; and straining sensation. The stool feature is measured by the Bristol Stool Form Scale (BSFS) [36], which classifies the form of human feces into seven types from separate hard lumps (type 1) to entirely liquid (type 7). Straining sensation measured in the range of 0–3 represents the intensity of difficulty during defecation, “0” means no difficulty, “1” means slight difficulty, “2” means medium difficulty, and “3” means much difficulty and assisted measures are needed for defecation.

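### Weekly SBMs size the trial but are never named primary, and six unranked efficacy outcomes are each tested at two-sided 0.05 with no control of error across them

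*Protocol article*

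**What the plan says.** The abstract names the stool diary, CCS, PAC-SYM and PAC-QoL together as the measures that "will be used to assess the clinical efficacy of different interventions". The Outcomes section divides the first of these: "The stool diary contains three domains: weekly SBMs; stool feature; and straining sensation". That makes six efficacy outcomes. The same section adds two mood scales (SAS, SDS) and heart rate variability. No outcome, contrast or time point is called primary or secondary.

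Only weekly SBMs enter the Sample size section: "We anticipate a mean weekly SBM improvement of 2.5 in the verum acupuncture group, 2.2 in the PEG 4000 group", then "1.8 in the sham acupuncture group, and 0.9 in the waiting-list control group". It concludes: "Considering α = 0.05, 1-β = 0.8, and a standard deviation of 2.0, a sample size of 128 is needed".

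The Clinical data analysis section applies a one-way ANOVA over four groups, Dunnett contrasts of group A with B, C and D, and paired t-tests within each group. For the diary and CCS it adds a repeated-measures ANOVA over three time points. All are read against one threshold: "The statistical significance threshold is set at 0.05 with the two-sided test".

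**The concern.** The first aim in the Background is to confirm the efficacy of verum acupuncture against sham and PEG 4000. With six unranked outcomes at the same threshold, the plan does not say which result settles that aim. The only multiplicity control, Dunnett, works within one outcome. A claim resting on any one of the six would therefore carry a false-positive risk above the nominal 5%, and a reader of the final report could not tell a planned main result from a favourable one among several.

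**Working it through.** **1. The plan's own figure.** Inputs from the Sample size section: means 2.5, 2.2, 1.8 and 0.9; SD 2.0; alpha 0.05; power 0.80; four equal groups.

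- Grand mean = 7.4/4 = 1.85. Squared deviations: 0.4225 + 0.1225 + 0.0025 + 0.9025 = 1.45.
- Cohen's f² = (1.45/4)/2.0² = 0.0906, so f = 0.301.
- Noncentral-F power of the four-group omnibus test: 79.9% at 31 per group and 81.3% at 32 per group. The smallest adequate total is 4 × 32 = 128, as stated.

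The trial is thus sized for an omnibus ANOVA on weekly SBMs and for no single contrast. The waiting list supplies 0.9025/1.45 = 62% of the between-group variation.

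**2. Error over outcomes, any contrast.** Dunnett holds the three contrasts within one outcome at 5%. Over six independent outcomes: 1 − 0.95⁶ = 26.5%.

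**3. Error over outcomes, one given contrast.** With three contrasts and 124 degrees of freedom, the Dunnett critical value is about 2.38. One contrast then has an error of about 1.9% per outcome. Over six independent outcomes: 1 − 0.981⁶ = 10.9%.

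**4. Correlated outcomes.** The document gives no correlations, so these are assumed. Simulation under no effect, 32 per group, a common correlation among the six outcomes, Dunnett within each:

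| Correlation | Any of three contrasts | One given contrast |
|---|---|---|
| 0 | 26% | 11% |
| 0.3 | 25% | 10% |
| 0.5 | 21% | 9% |
| 0.7 | 17% | 7% |
| 0.8 | 15% | 6% |

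The within-group paired tests and the mid-point are not counted. If the contrasts were read only after a significant ANOVA, the figures would be somewhat lower; the article states no such gate.

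**5. Power by contrast on weekly SBMs.** Normal approximation, 32 per group, standard error 2.0 × √(2/32) = 0.5. Sample size per group for 80% power = 2 × 2.0² × (1.960 + 0.842)²/difference².

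| Contrast | Difference | Power, unadjusted | Power, Dunnett | Per group for 80% (unadjusted) |
|---|---|---|---|---|
| Verum vs sham | 0.7 | 29% | 17% | 129 |
| Verum vs PEG 4000 | 0.3 | 9% | 4% | 698 |
| Verum vs waiting list | 1.6 | 89% | 79% | 25 |

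**The case against.** The best defence is that weekly SBMs are primary in all but name. They alone have stated expected means, an SD and a power, and N = 128 reproduces exactly as the first test in the analysis section. This stands in part: the outcomes are not on a fully equal footing. But the implied status has no effect in the analysis section, which treats all clinical data alike, and the missing designation is what leaves the error rate open.

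Several stronger readings go further than the document allows.

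- A reader might infer that the trial may be declared positive on whichever outcome succeeds. No such rule is written. The article only fails to exclude it, and the full protocol and supplementary files are not shown.
- A reader might apply the 26% to a given comparison such as verum versus sham. That overlooks Dunnett; the figure there is about 11% at most.
- A reader might count nine outcomes and quote 1 − 0.95⁹ = 37%. The abstract does not list SAS, SDS or heart rate variability among the efficacy measures.
- Independence is an upper bound. CCS includes items on defecation frequency and straining, which overlap two diary domains, so the higher correlations are the more plausible.
- A reader might say the diary and CCS are tested twice for one hypothesis. The repeated-measures ANOVA can equally be read as describing the time course. What is missing is a statement of which analysis decides.

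Nor is this a detail that an article normally leaves to an analysis plan. The article gives full outcome and analysis sections, with tests, contrasts and alpha, and the choice of primary outcome belongs with them.

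**Conclusion.** The point holds in a limited form. Weekly SBMs are the implied main outcome but are not designated, and six efficacy outcomes share one 0.05 threshold with error controlled only within each. The false-positive chance over the six is about three to five times nominal for any verum-versus-control contrast (15% to 26%), and about 1.2 to 2.2 times nominal for one given contrast (6% to 11%). These ranges rest on assumed common correlations from 0.8 down to 0, on 32 evaluable patients per group, and on no true effect on any outcome. The document does not support the view that any success may be claimed as a positive trial, nor that verum versus sham must be the sole primary contrast: the sample size matches the four-group test, and the first aim names both sham and PEG 4000.

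**What to change.** Designate change in weekly SBMs from baseline to end of treatment as the single primary outcome, tested by the four-group comparison with Dunnett contrasts already planned. State that this analysis decides, and that the repeated-measures ANOVA and the within-group paired tests do not. Make the other five efficacy outcomes and the mid-point secondary: either report them with confidence intervals and no confirmatory efficacy claim, or test them in a fixed order after the primary.

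The change is one of wording. The Trial status section reports 26 of 140 patients included, so it could be made well before unblinding. The price is the loss of confirmatory claims on the other scales.

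State also which contrast supports which claim, because the expected omnibus result comes largely from the waiting list. If verum versus sham is chosen to decide, disclose that the plan's own inputs (difference 0.7, SD 2.0) give about 29% unadjusted power at 32 per group, or about 17% with Dunnett, and that 80% unadjusted would need 129 per group. That shortfall exists already; naming the contrast only makes it visible.

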#### BOLD-fMRI data analysis

The BOLD-fMRI data will be processed and analyzed using SPM12 software (http://www.fil.ion.ucl.ac.uk/spm/) working on MATLAB 2013b (Mathworks, Inc., USA). The main analytical methods for cerebral responses of different interventions contain regional homogeneity (ReHo), amplitude of low frequency fluctuation (ALFF), and seed-based functional connectivity based on the results of ReHo and ALFF.

#### PET-CT data analysis

The SPM12 software will be applied to analyze the PET-CT data based on MATLAB 2013b. We will measure the whole brain radioactivity to present cerebral glucose metabolism and reflect the cerebral activity directly.

Furthermore, the results of BOLD-fMRI and PET-CT will be mutually verified and the imaging data will be associated with clinical data to investigate the possible correlation of brain activity changes elicited by different interventions with symptom improvements.

### Patient safety

In order to evaluate the risks caused by acupuncture and PEG4000, the blood routine test and blood biochemical test will be fulfilled again at the end of treatment. Adverse events such as bleeding, fainting, pain, infection, diarrhea, or other severe events will be recorded in the CRFs in detail and monitored by the Ethics Committees.

## Discussion

### The possibility of acupuncture modulating the abnormal cerebral activity to treat FC

The harmonious bidirectional interaction between the brain and the gut is a necessary prerequisite for retaining normal physiological function and homeostatic state of the gastrointestinal tract [43, 44]. Disharmony of the brain–gut axis might be a critical pathogenesis of FGIDs [26, 45]. Previous neuroimaging studies have found that the functional and/or structural abnormalities of the brain might be the highlighted pathological characteristics of FGIDs [46, 47]. For example, a systematic review of neuroimaging studies on FD found that abnormality of the pain and salience network was a key feature of FD [48]. Another review of irritable bowel syndrome (IBS) also reported that the changes occurring in the descending pain modulation system and the autonomic nervous system were relevant for IBS’s pathophysiology [49]. Furthermore, a resting-state fMRI study [50] performed on FC patients also found that brain regions implicated in emotional, somatic, and sensory processing, and motor control (such as supplementary motor area, dorsal anterior cingulate cortex) might contribute to the progression of FC.

Moreover, studies performed on individuals with FD [24], IBS [51], functional diarrhea [25], Crohn’s disease [52], and healthy controls [53] have found that having influence on the brain activity might be an important reason for modulating effects of acupuncture on gastrointestinal function. For example, our previous study [54] demonstrated that puncturing at ST36 could evoke homeostatic afferent processing network of FD patients, which was confirmed as a pivotal network of acupuncture treating for FD in another study [24]. Therefore, we hypothesize that acupuncture could treat FC through normalizing the pathological alteration of the brain activity.

